## Abstract

**Background:** Metabolic syndrome (MS) is a powerful risk factor for cardiovascular and cerebrovascular diseases. Although lifestyle intervention reduces several of the symptoms of the syndrome and cardiovascular risks, the lifestyle intervention that yields the benefits is restrictive. Jinlida is a Chinese patent medicine that has shown activity in type 2 diabetes, which has been approved in China. Preclinical studies in Jinlida granules support an improved role of abnormal glucose and lipids metabolism as well as reducing weight. Here, we describe the protocol of an ongoing clinical trial investigating a new therapy for metabolic syndrome in patients with abnormal glucose metabolism.

**Methods:** This study will enroll 880 subjects (aged 18–70 years) who have metabolic syndromes with abnormal glucose metabolism. All the participants in a double-blind, parallel, randomized, placebo-controlled trial, will receive Jinlida or placebo, orally, 9 g/time, three times daily for 2–4 years period on the basis of lifestyle intervention. The primary outcome measure (Incidence of type 2 diabetes) will be assessed during intervention cycles. Adverse events were monitored. All statistical tests will be performed using a two-sided test, and a *p* ≤ 0.05 (two-sided test) will be considered to be statistically significant results.

**Discussion:** Results from this study will provide evidence on whether incorporating oral Jinlida granules treatment into lifestyle intervention can delay or inhibit the development of diabetes mellitus in metabolic syndrome subjects with abnormal glucose metabolism.

**Clinical trial registration:** Registered at http://www.chictr.org.cn/enIndex.aspx. Trial registration number: ChiCTR1900023241.

## Background

The metabolic syndrome is a cluster of the most dangerous heart attack risk factors: diabetes and prediabetes, abdominal obesity, high cholesterol, and high blood pressure. The total risk of death was increased by a factor of 1.5 compared with non-metabolic syndrome (1). A cohort study from China demonstrated that the incidence of atherosclerosis cardiovascular disease (ASCVD) in subjects with metabolic syndrome was 3.12 times greater than those without metabolic syndrome (2). Additionally, as the global urbanization process accelerates, the population of metabolic syndrome further expands. According to data published by the International Diabetes Federation (IDF), a quarter of the world's population suffered from metabolic syndrome (3, 4). Importantly, especially in MS with diabetes and prediabetes, it contributed markedly to the development of ASCVD (5, 6).

Moreover, some studies have shown that 33% with impaired fasting glucose (IFG) and 71% with impaired glucose tolerance (IGT) also suffered from metabolic syndrome (7), which magnify the risk of ASCVD. As levels of blood glucose rises, even if the diagnostic criteria for diabetes (e.g., IFG, IGT) is not reached, the risk of ASCVD is still significantly increased (8–10). IGT is more common than IFG. Correspondingly, the risk of developing diabetes and cardiovascular disease in the IGT population is significantly higher than that of the IFG population (11). Daqing study demonstrated that ~90% of IGT subjects developed type 2 diabetes within 20 years, and half of them had at least one myocardial infarction or stroke event (12).

Urgent action to treat IGT in metabolic syndrome is especially necessary. Currently, the lifestyle intervention is widely recommended in clinical practice. Although active lifestyle intervention has been shown to be an effective strategy, the lifestyle intervention that yields the benefits is still restrictive and difficult to achieve in all the patients (13). Jinlida is a multitargeted antimetabolite that has shown activity in type 2 diabetes, which has been approved in China and consists of danshensu sodium salt, puerarin, salvianolic acid B, epimedin B, epimedin C, lcariin, and ginsenosides Rb1, Rc, and Rb2. The Jinlida, in one batch number, was manufactured by Shijiazhuang Yiling Pharmaceutical Co. (Shijiazhuang, China). Findings from pharmacological researches on Jinlida demonstrated its function protecting islet β-cell (14), anti-oxidative stress (15, 16), regulating hormones related with blood glucose (17), and protecting vascular endothelial cells (18). Additionally, Jinlida could reduce insulin resistance by regulating lipid metabolism (19, 20), promoting skeletal muscle gene and protein expression (21, 22), all of which play a key role in anti-metabolic disorders.

Our research team will implement a randomized, double-blind, placebo-controlled, and multi-center clinical trial to investigate the efficacy and safety of intervention with Jinlida granules in metabolic syndrome with abnormal glucose metabolism. This work describes the methodology and specific details underlying the study.

## Methods/Design

### Study objectives

In this study setting, the metabolic syndrome was defined as abdominal obesity, prediabetes (Impaired Glucose Tolerance), high cholesterol, and high blood pressure, not including diabetes. The aim of this study is to evaluate the effectiveness of Jinlida in delaying or inhibiting the development of diabetes mellitus in metabolic syndrome subjects with impaired glucose tolerance. We hypothesize that general lifestyle intervention + Jinlida granule is more effective than placebo + general lifestyle intervention in delaying or inhibiting the development of diabetes mellitus in metabolic syndrome subjects with impaired glucose tolerance. If successful, this work will provide clinical evidence for high-risk factors requiring intervention to prevent arteriosclerosis and inhibit the development of the cardiovascular pathology.

A total of 880 patients will be enrolled in this study over the course of 2 years. Recruitment takes place at an out-patient clinical institution. The principal investigators or investigators inform the patients (orally and in writing) about benefits and risks of participating in the study and of the clinical assessments and randomized allocation of treatment. Patients have to provide written consent before enrolling in the study. Patients may withdraw their consent to participate at any time without providing a reason. There is no financial compensation for the subjects. However, all clinical evaluations and study medication have no cost for the patients.

### Study Design

This study is designed as a randomized, double-blind, placebo-controlled, multicenter clinical trial with a ratio of 1:1, which includes 22 hospitals (Research Cooperation Center). The trial was registered at the Chinese Clinical Trial Registry (ChiCTR, www.chictr.org.cn); ID: ChiCTR1900023241, and any important changes in the protocol will be reflected there. Figure 1 shows the study flow.

**Figure 1 F1:**
[figure not shown]
The schedule of enrollment, interventions and assessments.

### Setting and Participants

This study will be conducted at 22 Collaborative Research Centers in China. Recruitment will be by advertisement in local free papers and by posters displayed in 22 Collaborative Research Centers as well as we disseminate relevant recruitment information in the community. The recruitment began in August 2019, and it will be completed within 2 years. All the participants will receive oral and written information regarding the study by a doctor involved in this work.

### Eligibility Criteria

#### Inclusion Criteria

Subjects are between 18 and 70 years of age;After the run-in period, subjects should meet the diagnostic criteria for metabolic syndrome (3, 6):

Indispensable indicators:Abdominal obesity (central obesity): waist circumference in male ≥ 90 cm, female ≥ 85 cm;Other indicators:At least two of the following four indicators can diagnose metabolic syndrome:① Hyperglycemia: fasting blood glucose (FBG) ≥ 6.1 or 2 h after glucose load (2HPG) ≥ 7.8 mmol/L and/or have been diagnosed as diabetes and received treatments.② Hypertension: blood pressure ≥ 130/85 mmHg and/or have been confirmed to be hypertension and received related treatments.③ Fasting TG ≥ 1.70 mmol/L.④ Fasting HDL-C <1.04 mmol/L.

3. After the run-in period, subjects should meet the diagnostic criteria for impaired glucose tolerance:(a) Impaired fasting glucose (IGT): FBG < 7.0 mmol/L and 2HPG: 7.8–11.1 mmol/L.

#### Exclusion Criteria

Subjects who have used hypoglycemic drugs in the past 3 months;Hyperthyroidism or hypothyroidism caused by endocrine disorders;Uncontrollable hypertension/hypotension: systolic blood pressure ≥200 mmHg or diastolic blood pressure ≥110 mmHg; or systolic blood pressure ≤ 90 mmHg, or diastolic blood pressure ≤ 60 mmHg;Comorbidities such as various acute infections, or severe infections, severe anemia, and neutropenia;Major disease comorbidities, such as active or untreated malignant tumors, or clinical remission of malignant tumors <5 years ago;Natural heart disease, such as congenital heart disease, rheumatic heart disease, hypertrophic or dilated cardiomyopathy, New York Heart Association (NYHA) cardiac function classification > III level;Subjects who had any of the following conditions within the past 6 months: coronary intervention (e.g., CABG or PTCA), stroke (including ischemic and hemorrhagic stroke);Severe liver and kidney dysfunction (ALT three times greater than the upper limit of the normal and creatinine >132 μmol/l);After the run-in period, fasting TG is <5.6mmol/L;Pregnant or lactating women, and women of childbearing age who have not taken effective contraceptive measures;Participation in any other clinical trials;For any reason, the investigator may consider a subject inappropriate for participation in this study.

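### The triglyceride item in the exclusion list, as written, admits only subjects with fasting TG of 5.6 mmol/L or more, which contradicts the inclusion criteria and the stated population

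*Protocol article*

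**What the plan says.** Under Exclusion Criteria, the protocol article includes the item "After the run-in period, fasting TG is <5.6mmol/L". No other section qualifies or corrects it.

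Under Inclusion Criteria, a subject needs central obesity by waist circumference, and then "At least two of the following four indicators can diagnose metabolic syndrome". The four are:

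- hyperglycaemia, which is met among other ways by "2 h after glucose load (2HPG) ≥ 7.8 mmol/L";
- "blood pressure ≥ 130/85 mmHg" or treated hypertension;
- "Fasting TG ≥ 1.70 mmol/L";
- "Fasting HDL-C <1.04 mmol/L".

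Separately, every subject must have impaired glucose tolerance (IGT) after the run-in: "FBG < 7.0 mmol/L and 2HPG: 7.8–11.1 mmol/L".

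Study objectives describes the population as people with metabolic syndrome and IGT. It sets no requirement for markedly raised triglycerides. Table 1 schedules blood lipids at the random enrolment visit (days −7 to 0), so a TG value is due when eligibility is decided.

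**The concern.** An item in an exclusion list removes those who meet it. This one removes subjects below 5.6 mmol/L and keeps those at or above it. The only admissible TG range then starts at more than three times the inclusion cut-off (5.6 / 1.70 = 3.3), in a trial whose inclusion rules do not require raised TG at all.

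Two things are at stake. If the 22 centres apply the item, the trial enrols a population that its objective does not describe, and nothing in the Sample Size Calculation ties the assumed 40% two-year control incidence to such a population. If they do not apply it, randomised subjects below 5.6 breach a written exclusion. Under Analysis Subjects, members of the per-protocol set (PPS) should generally be free of major protocol violations, so the make-up of that set could turn on how this line is read. Centres that read it differently would also enrol different populations.

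**Working it through.** The plan gives no figure to reproduce on this point. The check is one of logic, followed by an illustration of size.

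**Step 1: what IGT already supplies.** IGT requires a 2-hour glucose of 7.8 to 11.1 mmol/L. The hyperglycaemia indicator is met at 7.8 mmol/L or more. Every subject who satisfies the IGT criterion therefore has one of the four indicators and needs one more from blood pressure (BP), TG and HDL-C.

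**Step 2: enumerate the routes in.** Take waist circumference and IGT as met. Cross BP indicator (yes/no), HDL-C indicator (yes/no) and six TG values (1.0, 1.7, 3.0, 5.5, 5.6, 7.0 mmol/L): 2 × 2 × 6 = 24 combinations.

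| TG (mmol/L) | Combinations | Meet the Inclusion Criteria | Remain after the TG exclusion |
|---|---|---|---|
| 1.0 | 4 | 3 (all but BP no, HDL-C no) | 0 |
| 1.7, 3.0, 5.5 | 12 | 12 | 0 |
| 5.6, 7.0 | 8 | 8 | 8 |
| Total | 24 | 23 | 8 |

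These counts show the logic only. They are not proportions of patients.

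**Step 3: what the result means.** The barred groups are:

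- everyone with TG from 1.70 to below 5.6;
- everyone with TG below 1.70 who qualifies through BP or HDL-C.

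Everyone who remains has IGT and TG of at least 5.6, hence at least two indicators automatically. The 1.70 cut-off, the BP and HDL-C routes and the two-of-four rule then decide nothing. Two lists in which one makes most of the other redundant cannot both be as intended.

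**Step 4: how large the excluded share might be.** The documents give no TG distribution, so this step is an assumption. Let TG among otherwise eligible subjects be lognormal with median m and log-scale standard deviation s. The share admitted is

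P(TG ≥ 5.6) = 1 − Φ[(ln 5.6 − ln m) / s].

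| m (mmol/L) | s = 0.4 | s = 0.5 | s = 0.6 |
|---|---|---|---|
| 1.5 | 0.05% | 0.42% | 1.41% |
| 2.0 | 0.50% | 1.97% | 4.31% |
| 2.5 | 2.19% | 5.34% | 8.95% |
| 3.0 | 5.93% | 10.60% | 14.91% |

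For example, with m = 2.0 and s = 0.5: (ln 5.6 − ln 2.0) / 0.5 = 1.0296 / 0.5 = 2.059, and 1 − Φ(2.059) = 0.0197. Over the grid the admitted share runs from 0.05% to 14.9%, so the excluded share runs from about 85% to more than 99.9%.

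**The case against.** The strongest reply is that this is a slip in a journal article. The operative protocol, case report form and randomisation system are not shown, and sites may never have worked from this wording. That is fair as to what happened in the trial, and it limits what can be claimed. It does not remove the point. The article states an explicit numerical rule that conflicts with its own inclusion list, which is different from leaving detail to a fuller document. A fault in reading the file is also unlikely, because the other inequality signs in the same list make sense.

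A reader might infer several stronger things that the documents do not support:

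- **That every subject below 5.6 mmol/L meets an inclusion route.** A subject with TG below 1.70, untreated blood pressure below the cut-off and HDL-C of at least 1.04 has only the hyperglycaemia indicator and was never eligible.
- **That 880 subjects could not be found, or that nearly all those randomised are violators.** Both need a TG distribution and knowledge of site practice. The counts under Current Status (182 screened, 65 consented) do not help, because consent comes before the post-run-in TG check.
- **That the full analysis set would lose these subjects.** The wording under Analysis Subjects names violations of important inclusion criteria. This is an exclusion criterion, so only the PPS consequence follows.
- **That the liver and kidney item has the same fault.** It reads "ALT three times greater than the upper limit of the normal and creatinine" above a limit, which could be taken to require both. But the same list uses the word loosely to join alternatives elsewhere, for example in the item on pregnancy and contraception. That wording is at most ambiguous and forms no part of this point.

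**Conclusion.** The point holds. As written, the TG exclusion admits only subjects at or above 5.6 mmol/L, contradicts the Inclusion Criteria and does not match the population in Study objectives. That conclusion rests on the text alone and needs no assumption.

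The size does rest on an assumption: about 85% to more than 99.9% of otherwise eligible subjects excluded, under a lognormal TG distribution with median 1.5 to 3.0 mmol/L and log-SD 0.4 to 0.6. The PPS consequence is conditional. It arises if sites did not apply the item and if the breach is classed as major.

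The article does not show how the error arose. The inequality may be reversed, or a condition for entry may have been put in the exclusion list. Because this is an operative eligibility threshold and the correction is cheap, it must be fixed.

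**What to change.** 1. Compare the TG item with the ethics-approved protocol, the case report form and the eligibility check in the randomisation system. Establish whether the inequality is reversed or an entry condition was placed in the wrong list, and reconcile the item with the Inclusion Criteria accordingly.
2. Issue an erratum to the article and update the registry entry.
3. If the approved protocol or the system carries the same wording, correct it there through the usual amendment route.
4. Document, before unblinding, how subjects already randomised with TG below 5.6 mmol/L are classified for the PPS. Do not declare them free of violation in advance: if the approved text reads as the article does, they are deviations and must be recorded as such.

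The cost is a document check, an erratum and a registry update, plus an amendment if the source text is also wrong. No extra subjects are needed, and the sample-size arithmetic is unaffected because it contains no TG term.

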### Sample Size Calculation

According to “Lian et al. (23),” after 1 year of follow-up, the average annual incidence of diabetes in the placebo group was 29.32%. “Gao et al. (24)” demonstrated a cumulative incidence of diabetes in placebo group after 3 years of follow-up was 43.86%.

Our hypothesis assumes that the incidence of diabetes in the control group would be 40.0% after 2 years of intervention and the HR would be expected to be 0.75—the study drug is predicted to reduce the risk by 25%—employing α = 0.05, β = 0.20. The study group and the control group will be allocated in a 1:1 ratio. The study period will last 4 years, including 2 years of medication treatment and 2 years of follow-up. PASS16 software will be employed to calculate the sample size, each group should contain 395 subjects. Considering a 10% the violation rate and issues of inter-center case allocation, a total of 880 cases and evaluation of number of endpoint events 209:171 will be required to reach statistical significance.

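### As printed, the triglyceride exclusion admits only subjects with fasting TG of at least 5.6 mmol/L, which conflicts with the metabolic syndrome population defined elsewhere in the protocol

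*Protocol article*

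**What the plan says.** All references are to the protocol article.

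- **Exclusion Criteria.** One item reads "After the run-in period, fasting TG is <5.6mmol/L". The neighbouring items each name a state that bars entry, such as recent hypoglycaemic drugs, creatinine above a limit, or pregnancy.
- **Inclusion Criteria, metabolic syndrome.** Central obesity is mandatory. Beyond that, "At least two of the following four indicators can diagnose metabolic syndrome": hyperglycaemia, raised blood pressure, "Fasting TG ≥ 1.70 mmol/L", and low HDL-C. Raised TG is therefore optional.
- **Inclusion Criteria, glucose.** Impaired glucose tolerance (IGT) after run-in is mandatory: "FBG < 7.0 mmol/L and 2HPG: 7.8–11.1 mmol/L". The hyperglycaemia indicator is already met by "2 h after glucose load (2HPG) ≥ 7.8 mmol/L".
- **Study objectives.** The aim concerns "delaying or inhibiting the development of diabetes mellitus in metabolic syndrome subjects with impaired glucose tolerance". The definition of metabolic syndrome given there names abdominal obesity, prediabetes, cholesterol and blood pressure, and sets no TG requirement.
- **Study objectives, enrolment.** "A total of 880 patients will be enrolled in this study over the course of 2 years".
- **Analysis Subjects.** The per-protocol set (PPS) requires, among other things, that there be no major protocol violation. The examples of exclusions from the full analysis set (FAS) refer to breaches of important inclusion criteria.

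**The concern.** An item in an exclusion list bars whoever meets it. Here that means everyone with TG below 5.6 mmol/L, including subjects whose TG lies between 1.70 and 5.6 and who qualify for metabolic syndrome partly on that value. It also bars those with normal TG who qualify through blood pressure or HDL-C. What remains is a group defined by high TG, which no other part of the article describes.

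Either way of running the trial has a cost. If sites follow the text, the trial studies a different and narrower population than the one in its title and aim, and recruitment becomes much harder. If sites follow the presumed intention, most participants breach a written eligibility criterion, and someone must later decide whether that is a major violation for the PPS. In both cases a reader cannot tell from the article who was eligible, although recruitment had already begun.

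**Working it through.** The protocol attaches no figure to this criterion, so there is none to reproduce. The check has two parts: the logic of the two lists, which uses only the protocol, and the share of subjects affected, which needs an assumption.

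**1. Logic of the lists**

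Inputs: central obesity met; IGT met (2-hour glucose 7.8–11.1 mmol/L), so the hyperglycaemia indicator is always met; blood pressure indicator yes or no; HDL-C indicator yes or no.

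Indicators met = 1 (glucose) + [blood pressure] + [TG ≥ 1.70] + [HDL-C]; at least 2 are required.

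Number of the four blood pressure/HDL-C combinations that are eligible:

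| Fasting TG (mmol/L) | Exclusion as printed (TG < 5.6 excluded) | Opposite sign (TG ≥ 5.6 excluded) |
|---|---|---|
| 1.2 | 0 of 4 | 3 of 4 |
| 1.7 | 0 of 4 | 4 of 4 |
| 2.5 | 0 of 4 | 4 of 4 |
| 5.5 | 0 of 4 | 4 of 4 |
| 5.6 | 4 of 4 | 0 of 4 |
| 7.0 | 4 of 4 | 0 of 4 |

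As printed, eligibility depends on TG ≥ 5.6 alone. Anyone who passes already has 1 (glucose) + 1 (TG) = 2 indicators, so the two-of-four rule, the 1.70 threshold and the blood pressure and HDL-C indicators remove nobody. With the opposite sign they work again: at TG 1.2 a subject needs raised blood pressure or low HDL-C to qualify. The right-hand column is a logic check and does not establish what the sponsor intended.

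**2. Share of subjects affected**

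The article gives no TG distribution. Assumption: log-normal among otherwise eligible subjects, with median m from 1.5 to 3.0 mmol/L and log-scale SD s from 0.4 to 0.7.

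Share with TG ≥ 5.6 = 1 − Φ((ln 5.6 − ln m)/s). Number of otherwise eligible people needed to find 880 = 880 / share.

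| m | s | (ln 5.6 − ln m)/s | Share ≥ 5.6 | Share excluded as printed | Needed for 880 |
|---|---|---|---|---|---|
| 1.5 | 0.4 | 3.29 | 0.05% | 99.95% | about 1.8 million |
| 2.0 | 0.5 | 2.06 | 1.97% | 98.0% | about 44,600 |
| 2.5 | 0.5 | 1.61 | 5.34% | 94.7% | about 16,500 |
| 3.0 | 0.7 | 0.89 | 18.6% | 81.4% | about 4,700 |

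The first and last rows are the extremes of the grid. The counts use unrounded shares. Every assumption tried excludes a large majority, but the exact share and the counts depend on the assumption.

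**The case against.** The strongest reply is that this is a slip in a condensed article. Investigators would probably query so implausible a rule, the full protocol may have it right, and nothing shows that any site applied the printed text. That is fair, and it means the harms above are conditional. It does not remove the point: the criterion is stated outright and is wrong as it stands against the inclusion list and the aim.

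A reader might infer several stronger things that the article does not support:

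- **That the two lists contradict each other outright.** They do not. A subject with central obesity, IGT and TG of 5.6 or more satisfies both. The defect is that the exclusion makes the optional indicators idle and changes the population. One of them, hyperglycaemia, is idle in any case because IGT is mandatory.
- **That the sign is certainly reversed.** This is the most natural reading, but the intended criterion appears nowhere. A misplaced inclusion item or an error made only in the article would look the same.
- **That affected subjects would drop out of the FAS.** The FAS wording names inclusion criteria, and this item is an exclusion criterion. Only the PPS clause on major violations plausibly applies.
- **That 880 subjects could not be recruited.** This depends on the assumed distribution, and the grid gives no firm floor.
- **That the error is built into the randomisation system or the case report form.** The Randomization section mentions only name, age and gender being entered, and no TG check is described anywhere.

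The Current Status counts (182 screened, 65 consented by May 2020) settle nothing. Consent comes at run-in and lipids are measured at the later enrolment visit, so these counts precede the criterion.

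**Conclusion.** The point holds. On the text alone, with no assumption, the printed exclusion limits entry to TG of at least 5.6 mmol/L, leaves the two-of-four rule with nothing to do, and conflicts with the population in the abstract, the objectives and the Inclusion Criteria. The size is indicative only: roughly 80% to over 99% of otherwise eligible subjects excluded, under log-normal assumptions not drawn from the protocol. Which correction is intended remains an inference, and there is no evidence that the wrong subjects were enrolled. Correction is nevertheless necessary, because the line determines who may enter.

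**What to change.** 1. Reconcile the Inclusion and Exclusion Criteria on TG against the full approved protocol and the registry record, and confirm the intended criterion.
2. Correct the line so that it is consistent with the inclusion list. If the intention is as presumed, either reverse the inequality or move the item, as worded, to the inclusion list. Written as TG ≥ 5.6 in the exclusion list or TG < 5.6 in the inclusion list, the two give the same population. A reversal written as strictly above 5.6 would differ only at exactly 5.6, so the boundary should be explicit.
3. Carry the correction into any trial document that repeats the line.
4. Check the post-run-in TG of subjects already entered against the confirmed criterion, and state how any breach is handled for the PPS.

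The cost is a one-line correction, an update to the registry record if it carries the same line, and a check of existing records. Table 1 already schedules blood lipids at the enrolment visit, so no new tests or patients are needed.
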